**FIGURE 1 brb370631-fig-0001:**
[figure not shown]
Flow diagram of the study.

The sample size for this study will be calculated using the formula for a superiority trial of two independent sample sizes. Clinical experience and preliminary research indicated an effective rate of 90% in the treatment group and 80% in the control group (Hei et al. 2023, Su et al. 2023, Zhang et al. 2023). Based on these data, we conducted a sample size calculation using a two‐tailed *t*‐test with the following parameters: test boundary value *δ* = 0.15, significance level *α* = 0.025, and power *β* = 0.20 (Zabor et al. 2020). The calculation was performed using the following formula.

$$n=\left[{\left(Z_{\alpha /2}+Z\beta \right)}^{\wedge 2}*\left(p1\left(1-p1\right)+p2\left(1-p2\right)\right)\right]/{\left(\delta -|p1-p2|\right)}^{\wedge 2}$$

Considering a case number ratio of k = 1 between groups, the calculated sample size was 32 cases per group. To account for a potential 10% dropout rate, we increased the sample size to approximately 35 cases per group (International Council for Harmonisation of Technical Requirements for Pharmaceuticals for Human Use 1998). The total sample will be divided into 6 groups: control, EA, HOT, combination therapy, sham therapy, or the healthy, totaling around 210 cases to be included.

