### Data Analysis

2.11

Researchers who are blind to the groupings will conduct data management and statistical analysis on the data acquired using the statistical software SPSS 22.0 (SPSS Inc., Chicago, IL, United States). Descriptive statistics will be utilized to depict the baseline characteristics of the two participant groups, with mean ± standard deviation for normally distributed continuous data and median and quartiles for non‐normally distributed continuous data. The normality of the data will be assessed using the Shapiro–Wilk test, and the homogeneity of variance will be assessed using the Levene test. One‐way analysis of variance (ANOVA) will be used for comparisons among multiple groups for normally distributed continuous data, while repeated measures analysis of variance will be used for within‐group pre‐ and post‐treatment comparisons. The Kruskal–Wallis test will be employed for non‐normally distributed continuous data. The significance level (α) for the statistical hypothesis tests will be set at *p* < 0.05, one‐tailed.

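### Section 2.11 tests at 0.05 one-tailed while section 2.1 plans with two-tailed 0.025, and one-tailed has no directional meaning for the between-group omnibus tests

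*Protocol article*

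**What the plan says.** Two sections of the protocol article set a significance rule.

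- **Section 2.1, Objectives and Sample Size.** The text says "we conducted a sample size calculation using a two‐tailed *t*‐test with the following parameters", and those parameters include "significance level *α* = 0.025, and power *β* = 0.20". The 0.20 is evidently the type II error, so power is 80%. The printed formula uses the critical value for alpha/2, which fits a two-tailed test. The other inputs are an "effective rate of 90% in the treatment group and 80% in the control group" and a "test boundary value *δ* = 0.15", and the stated result is that "the calculated sample size was 32 cases per group".
- **Section 2.11, Data Analysis.** The closing sentence says that the level for hypothesis tests "will be set at *p* < 0.05, one‐tailed". The tests named just before it are one-way ANOVA for comparing several groups, repeated measures ANOVA for changes within a group, and Kruskal–Wallis for non-normal data.

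The Aims paragraph of the abstract and the end of the Introduction add a directional goal: to show that the combination is superior to either treatment alone.

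**The concern.** The rule that decides whether the primary MoCA result counts as significant is given twice, with a different level and a different number of tails. This is not detail left to an analysis plan that is not shown: both rules are printed, and they cannot both hold.

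The analysis rule also does not fit the between-group tests beside it. With more than two groups, the F and Kruskal–Wallis statistics reject in their upper tail, but they respond to differences in any direction. An analyst told to work one-tailed has no direction to apply.

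The rule does take effect on directional comparisons such as combination versus monotherapy. There it would accept favourable results that a two-sided 0.05 test would not. It also leaves no way to declare an arm worse than its comparator, which matters because section 2.6.1 describes the control arm as drug-treated.

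**Working it through.** **Step 1: which alpha lies behind the planned 32 per group?** Inputs from section 2.1: p1 = 0.90, p2 = 0.80, delta = 0.15, power 80% (z = 0.8416), allocation 1:1. The variance term is 0.90 × 0.10 + 0.80 × 0.20 = 0.25. The printed formula is n = (z_alpha + z_beta)² × 0.25 / (delta − |p1 − p2|)², with denominator 0.05² = 0.0025. The last column replaces that denominator by (delta + |p1 − p2|)² = 0.25² = 0.0625.

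| Alpha rule | z_alpha | n, printed denominator | n, denominator 0.0625 |
|---|---|---|---|
| two-tailed 0.025 (as written in 2.1) | 2.2414 | 950.5 → 951 | 38.02 → 39 |
| two-sided 0.05, or one-sided 0.025 | 1.96 | 784.89 → 785 | 31.40 → **32** |
| one-sided 0.05 (as in 2.11) | 1.6449 | 618.26 → 619 | 24.73 → 25 |

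The printed formula does not give 32 under any of these rules. Among the variants tried, 32 appears only with z = 1.96 and the sign in the denominator changed. So the planned alpha is itself uncertain: the text says two-tailed 0.025, while the stated number fits two-sided 0.05 or one-sided 0.025.

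**Step 2: error rate of the analysis rule against each planned alpha.**

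| Reading of the rule in 2.11 | Error as analysed | Against two-tailed 0.025 | Against z = 1.96 (two-sided 0.05) |
|---|---|---|---|
| Omnibus test, p < 0.05 read as usual | 5% | 5/2.5 = 2× | 5/5 = 1× |
| Directional contrast, total error | 5% | 5/2.5 = 2× | 5/5 = 1× |
| Directional contrast, favourable direction only | 5% | 5/1.25 = 4× | 5/2.5 = 2× |
| Omnibus p-value halved (not stated in the plan) | 10% | 10/2.5 = 4× | 10/5 = 2× |

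**Step 3: check of the omnibus rows.** One-way ANOVA was simulated with equal means, 32 per group, 40,000 runs. The usual rule p < 0.05 rejected in 0.048 of runs with five groups and 0.051 with six. Halving the p-value first gave 0.099 and 0.098.

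**Step 4: what changes for a directional contrast.** A favourable result is significant one-tailed at 0.05 when its two-sided p is below 0.10. The results affected are therefore the favourable ones with two-sided p between 0.05 and 0.10.

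**The case against.** The strongest reply is that little goes wrong in practice. If one-tailed means nothing for a multi-group test, the analyst reads the ordinary omnibus p-value at 0.05 and the error is about 5%. The words might even be a loose description of the upper-tail rejection of the F statistic. Section 2.11 names no pairwise test, so the directional harms arise only in follow-up contrasts that it does not describe. All of this stands, and it limits the size of the point. It does not remove the conflict between the two sections, and the stated aim of superiority over monotherapy does call for such contrasts.

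A reader might infer more than the document supports in three ways:

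- **That the false-positive rate is simply 2 to 4 times the planned one.** The ratio is 1 for an ordinary omnibus test set against two-sided 0.05. A ratio of 4 needs either a count of the favourable direction alone or a halved omnibus p-value.
- **That the plan would halve omnibus p-values or choose a direction after seeing the data.** No section says so, and for combination versus monotherapy the direction is given in advance by the aim.
- **That none of the named tests has a one-tailed form.** TCD, fNIRS, fMRI and STAI are measured only at baseline and week 4 (Table 2). For a within-group comparison of two time points the F test has one numerator degree of freedom and equals t², so a one-sided version exists. The statement that one-tailed is undefined is safe for the between-group tests.

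**Conclusion.** The point holds as an inconsistency in a stated decision rule. Level and sidedness differ between sections 2.1 and 2.11, and the one-tailed rule is undefined for the between-group ANOVA and Kruskal–Wallis tests.

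Its size is 1 to 4 times the planned false-positive rate, and the document does not settle where in that range it falls. That depends on two assumptions: whether the planned alpha is the written two-tailed 0.025 or the z = 1.96 that fits 32 per group, and whether the conclusion rests on an omnibus test or on a directional contrast. For directional contrasts alone, the error in the favourable direction is 2 or 4 times the planned one.

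**What to change.** Replace the last sentence of section 2.11 with: *Omnibus tests use alpha 0.05; all pairwise contrasts are two-sided at 0.05 with 95% confidence intervals.* State the same two-sided 0.05 in section 2.1. This should be settled before the data are analysed.

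Two-sided 0.05 is looser than the 0.025 now written in 2.1, but it has the critical value that fits the stated 32 per group.

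The cost is one sentence in 2.11, the alpha statement in 2.1, and some power for directional contrasts compared with one-tailed 0.05. As an illustration, take the variant of the formula that gives 32, with denominator 0.0625. The standardised effect at n = 32 is 0.25/√(0.25/32) = 2.828. Power is then Φ(2.828 − 1.645) = 88% one-tailed and Φ(2.828 − 1.960) = 81% two-sided. These figures rest on that variant, not on the printed formula.

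Changing alpha does not repair section 2.1. The printed formula gives 785 per group at two-sided 0.05 and 951 at two-sided 0.025, so its failure to yield 32 needs its own correction.

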## Discussion

3

PSCI is a form of cognitive dysfunction that can occur following a stroke. Two non‐pharmacological treatment methods that have gained attention for their minimal side effects are traditional Chinese medicine olfactory inhalation therapy and electric neck acupuncture. Electric acupuncture has been widely used in treating neurological conditions like cerebral ischemia, Alzheimer's disease, and Parkinson's disease (Cai et al. 2019, Shin et al. 2017, Kong et al. 2010). Electric neck acupuncture, a novel technique developed by [name], leverages the anatomical, physiological, and pathological features of the neck to treat neurological disorders effectively (Liu et al. 2017). While there is limited research on the efficacy of electric neck acupuncture for PSCI, TCM olfactory inhalation therapy focuses on enhancing cognitive function and emotional well‐being by stimulating the olfactory nerve in brain regions associated with the sense of smell. Ancient texts like the Divine Farmer's Materia Medica mention the therapeutic benefits of olfactory inhalation therapy for conditions such as senile dementia, stroke, and epilepsy. HOT works through the aroma molecules of plants, which are transmitted to the limbic system of the brain and even through the pores of the human body, penetrating into the deeper tissues, resulting in muscle relaxation and a pleasant emotional feeling. Studies have shown that the use of calamus volatile oil by gavage for three weeks can reduce nitric oxide synthase (NOS) in the brain and hippocampus of Alzheimer's disease mouse models, and significantly improve learning and memory dysfunction (Tian et al. 2012). Inhalation of eugenol over a 4‐week period enhanced learning memory by interfering with neurotransmitters in the olfactory system, thereby altering olfactory afferent signals (Shuai et al. 2021). Our study aims to explore the potential of traditional Chinese medicine olfactory inhalation therapy and electric neck acupuncture, either individually or in combination, as treatments for PSCI.

Our research aims to evaluate the improvement of cognitive function in individuals with PSCI using different treatment methods. We have selected MoCA as the primary outcome measure for this study. MMSE and MBI is used as secondary outcome measures. The MoCA is another rapid screening tool for cognitive impairment, particularly sensitive to mild to moderate impairments, covering a wider range of cognitive domains comprehensively (Pinto et al. 2019). It includes more extensive memory tests by increasing the number and difficulty of words, extending the delay in recall, and providing a more accurate reflection of participants’ memory status. However, it requires more time compared to the MMSE. The MMSE is the most widely used dementia screening scale globally, focusing on cognitive abilities including orientation, memory, attention, calculation, recall, and language. It is a simple tool that aids in initial screening and categorizes participants based on their education level, with higher scores indicating stronger cognitive abilities, classified as normal, mild cognitive impairment, and dementia (Creavin et al. 2016). The ultimate goal of improving cognitive function is to reintegrate patients into their families and society. The MBI assesses daily living abilities in areas such as grooming, bathing, feeding, toileting, dressing, bowel and bladder control, stair climbing, transferring, walking on level surfaces, and wheelchair use. It provides different levels of ratings and reflects participants’ capabilities in daily activities (Liu et al. 2020).

In addition to the primary outcome measures, we also included some imaging examinations as secondary measures. fMRI is used to assess cerebral hemodynamics and identify activated brain regions to compare different groups (Logothetis 2008). fNIRS is a non‐invasive, portable, and cost‐effective method that measures changes in oxygenated and deoxygenated hemoglobin levels in the cerebral cortex using near‐infrared light, reflecting neural activity (Irani et al. 2007). fNIRS allows for convenient self‐control and observation of the brain during treatment, providing detailed insights into stimulated brain areas by acupuncture and Traditional Chinese medicine olfactory. Ultrasound Doppler is another non‐invasive method to examine cerebrovascular diseases by detecting hemodynamic and physiological changes in major intracranial arteries (Wan et al. 2022). These secondary measures help us understand participants' cerebral vascular function changes during treatment and offer preliminary evidence for further exploration of underlying mechanisms. Moreover, by comparing with the healthy population, this study more clearly revealed the abnormal brain function of patients with cognitive impairment after stroke and the effect of intervention on their brain function. This design not only enhances the scientific validity of the study results, but also provides a more reliable basis for clinical application.

The study design was limited to a single‐center study, resulting in a relatively small sample size. To enhance the robustness of the study, future studies should include more diverse cases from multiple centers. Additionally, the lack of a sham stimulation group as a control group due to controversies surrounding the need for sham acupuncture and its implementation is a limitation of this trial design. Subsequent experiments will delve into detailed basic research both in vitro and in vivo to uncover the molecular mechanisms behind HOT and EA treatment for enhancing cognitive function in stroke patients. While non‐pharmacological treatments show promise in addressing PSCI injuries, further extensive research and clinical trials are essential to validate their efficacy and safety. Therefore, the significance of this study lies in providing stronger evidence for the clinical application of these treatments.

## Ethics Statement

The study protocol was approved by the Institutional Review Board of the Affiliated People's Hospital of Hangzhou Medical College (KT2024016) and was registered at https://register.clinicaltrials.gov (NCT06313866), and registered on March 21, 2024.

## Consent

Informed consent was obtained from all individual participants included in the study.

## Peer Review

The peer review history for this article is available at https://publons.com/publon/10.1002/brb3.70631.

## Data Availability

The data that support the findings of this study are available upon request from the corresponding author, upon reasonable request.
